**9.1.2.16 Incidence of COVID-19 Requiring ICU Occurring Post First Dose of Study Intervention**

An event is defined as COVID-19 Requiring ICU in [Table 6](#) and with both admission date and onset date of associated COVID-19 are post first dose of study intervention.

**9.1.2.17 Incidence of COVID-19 Requiring ICU Occurring  $\geq$  22 Days Post First Dose of Study Intervention**

An event is defined as COVID-19 Requiring ICU in [Table 6](#) and with both admission date and onset date of associated COVID-19 are  $\geq$  22 days post first dose of study intervention.

**9.1.2.18 Secondary Efficacy Endpoint Based on Nucleocapsid Antibody: Detection of SARS-CoV-2 Nucleocapsid Antibody Levels Over Time**

If data available, the detection of SARS-COV-2 nucleocapsid antibody will be summarised as proportion of participants who have a post-treatment response (negative at baseline to positive post treatment with study intervention) to SARS-CoV-2 Nucleocapsid antibodies. This will be summarized by study arm, by visit, overall and by PCR result based on analysis sets for immunogenicity. The window conventions defined in [Table 5](#) will apply to this variable.

## **9.2 Efficacy Analyses**

The efficacy analyses will be conducted in the analysis sets as planned in [Table A1](#)[Table 3](#), unless otherwise specified.

## 9.2.1 Primary Efficacy Analyses

### 9.2.1.1 Pooled Analysis of Primary Efficacy Endpoint

A Poisson regression model with robust variance (Zou 2004) will be used as the primary efficacy analysis model to estimate the relative risk (RR) of the incidence of SARS-CoV-2 virologically-confirmed primary symptomatic COVID-19 between the AZD1222 and control groups. The model contains the term of study code, treatment group, and age group at randomization (ie, 18-55 years, 56-69 years, and  $\geq 70$  years). The logarithm of the period at risk for primary endpoint for pooled analysis will be used as an offset variable in the model to adjust for volunteers having different follow up times during which the events occur.

Vaccine efficacy (VE), which is the incidence of infection in the vaccine group relative to the incidence of infection in the control group expressed as a percentage, will be calculated as  $VE = 1 - \text{relative risk}$ . The VE, and its corresponding 2-sided  $(1-\alpha)$  % confidence interval (CI), will be estimated from the model. In addition, the 2-sided p value testing null hypothesis that the incidence of SARS-CoV-2 virologically-confirmed primary symptomatic COVID-19 between AZD1222 and control groups are the same will be obtained from the model. Statistical significance will be achieved if the 2-sided p value is  $\leq \alpha$ , where  $\alpha$  for interim and primary analysis as described in Section 4.1.

The Poisson regression with robust variance analysis will be implemented by using the SAS PROC GENMOD procedure for binary data with the REPEATED statement for subject ID and logarithm link. The estimated parameter  $\hat{\beta}$  [ie,  $\log(\widehat{RR})$ ], 2-sided  $(1-\alpha)$  % CI for  $\hat{\beta}$ , and the 2-sided p value will be obtained from the SAS outputs. The estimated RR and corresponding CI for the RR is given by exponentiating  $\hat{\beta}$  and its confidence limits. Therefore, the percent of VE is given by  $[(1 - \exp(\hat{\beta})) * 100\%]$ . The CI for the percent of VE is given by  $[(1 - \exp(\text{upper confidence limit for } \hat{\beta})) * 100\%, [1 - \exp(\text{lower confidence limit for } \hat{\beta})) * 100\%]$ .

If the Poisson regression model with robust variance fails to converge, the exact conditional method for stratified Poisson regression using PROC GENMOD with the exact statement will be used.

To investigate if the pooled studies are homogeneous, a study-by-treatment interaction term may be included in the Poisson regression model as a factor and the type III p value for this term will be presented. If the p value is greater than or equal to 0.05, the study-by-treatment interaction term may be dropped from the model for presentation of summary analysis results. Same method may be performed for dose schedule ( $< 6$  weeks, 6-8 weeks, 9-11 weeks, 12+ weeks), and dose pattern (LD/SD, SD/SD) if further exploration is warranted.

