## 4.1 Planned Analyses

The proposed primary and interim pooled analyses provide an opportunity to produce early and robust estimates of efficacy to support rapid decision making in the present conditions of

this public health emergency. One interim analysis and one primary analysis are planned as below:

The interim analysis will be triggered when 53 COVID-19 cases (SARS-CoV-2 virologically confirmed) that occurred  $\geq 15$  days post the second dose have been reported in participants who received SD/SD (as defined in [Table 4](#)) across the AZD1222 and control groups in pooled studies. This would provide 77% power for the 20% threshold to assume a true vaccine efficacy of 70%. The analysis will include participants who received two doses, with a SD as the second dose (ie, participants who received LD/SD or SD/SD). For an individual study to be included in the pooled analysis of efficacy, a minimum of 5 primary endpoint defined cases must be accrued. For COV002, only cases accruing in efficacy study groups will be included (groups 4, 6, 9, 10).

The primary analysis will be triggered when 105 COVID-19 cases (SARS-CoV-2 virologically confirmed) that occurred  $\geq 15$  days post the second dose have been reported in participants who received SD/SD (as defined in [Table 4](#)) across the AZD1222 and control groups. This would provide 90% power for the 20% threshold to assume a true vaccine efficacy of 60%. The analysis will include participants who received two doses, with the second dose being SD (ie, participants who received LD/SD or SD/SD). For an individual study to be included in the pooled analysis of efficacy, a minimum of 5 primary endpoint defined cases must be accrued. For COV002, only cases accruing in efficacy study groups will be included (groups 4, 6, 9, 10).

Gamma Alpha-Spending function is used to control the overall Type 1 Error at 5%. The planned alpha level is 1.13% for interim analysis and 4.44% for primary analysis. The minimum observed VE if an interim or primary analysis demonstrates evidence of efficacy is 64% and 48%, respectively.

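### The written success rule tests VE = 0, but the stated power and minimum VE belong to a VE > 20% criterion; at the primary analysis the written rule passes at about 33% observed VE, not 48%

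*SAP*

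**What the plan says.** **Design figures (SAP Section 4.1).** "The interim analysis will be triggered when 53 COVID-19 cases", counted in SD/SD recipients, and "The primary analysis will be triggered when 105 COVID-19 cases" on the same basis. For the interim: "This would provide 77% power for the 20% threshold to assume a true vaccine efficacy of 70"%. For the primary analysis: "This would provide 90% power for the 20% threshold to assume a true vaccine efficacy of 60"%. The nominal levels follow: "The planned alpha level is 1.13% for interim analysis and 4.44% for primary analysis". The section then turns the design into observed results: "The minimum observed VE if an interim or primary analysis demonstrates evidence of efficacy is 64% and 48%, respectively".

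**Success rule (SAP Section 9.2.1.1).** The Poisson model yields VE, a two-sided (1-alpha) CI and a "2-sided p value testing null hypothesis that the incidence of SARS-CoV-2 virologically-confirmed primary symptomatic COVID-19 between AZD1222 and control groups are the same". Significance is reached if that p value does not exceed the Section 4.1 alpha. The CI is to be reported, but no condition is placed on its lower limit.

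Sections 7.1 and 9.1 carry forward the alpha split only. The 20% threshold does not reappear as a null value or a CI criterion in Sections 7.1, 9.1 or 9.2.

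**The concern.** The two sections imply different hurdles. A threshold of 20%, with a power and a minimum VE attached to it, points to a null of VE at most 20% (RR at least 0.80). The rule in Section 9.2.1.1 tests RR = 1. If the Section 4.1 figures come from the first null, they do not describe the test that will be run.

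A range of results would then count as success under Section 9.2.1.1 while falling short of the minimum in Section 4.1. This is the primary efficacy claim of a pooled analysis prepared for a marketing authorisation application. Which hurdle applies should not be left to be argued once the result is known.

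**Working it through.** **Inputs from the SAP.** Cases D = 53 and 105; alpha = 0.0113 and 0.0444 (Section 4.1), two-sided (Section 7.1); threshold VE 20%; assumed true VE 70% (interim) and 60% (primary).

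**Assumption.** Equal person-time in the two groups, because the SAP gives no allocation ratio. Other ratios are tried below.

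**Method.** Let x be the number of vaccine-group cases among D.
- Observed VE = 1 − x/(D − x).
- Under a true VE, x is binomial with p = (1 − VE)/(2 − VE).
- SE of log RR = √(1/x + 1/(D − x)).
- Success means the upper (1-alpha) limit for RR is at or below 1 − VE0, where VE0 is the null value.
- Critical values are z = 2.533 (alpha 0.0113) and z = 2.010 (alpha 0.0444).

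**Step 1: reproduce Section 4.1 with VE0 = 20% (upper limit for RR at most 0.80).**
- Interim, x = 14: RR = 14/39 = 0.359, SE = 0.312, upper limit 0.790, pass. At x = 15 the limit is 0.855, fail. Minimum VE = 64.1%. Power at VE 70%, with p = 0.3/1.3, is P(x ≤ 14) = 77.4%.
- Primary, x = 36: RR = 36/69 = 0.522, SE = 0.206, upper limit 0.789, pass. At x = 37 the limit is 0.820, fail. Minimum VE = 47.8%. Power at VE 60%, with p = 0.4/1.4, is P(x ≤ 36) = 91.8%.

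The exact conditional binomial test gives the same two cut-offs.

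**Step 2: the rule as written, VE0 = 0 (upper limit for RR at most 1).**
- Interim, x = 17: RR = 17/36 = 0.472, SE = 0.294, upper limit 0.995, pass. x = 18 fails (1.072).
- Primary, x = 42: RR = 42/63 = 0.667, SE = 0.199, upper limit 0.995, pass. x = 43 fails (1.034).

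| | Section 4.1 states | VE0 = 20% | VE0 = 0 |
|---|---|---|---|
| Minimum VE, interim | 64% | 64.1% | 52.8% |
| Minimum VE, primary | 48% | 47.8% | 33.3% |
| Power at VE 70%, interim | 77% | 77.4% | 95.3% |
| Power at VE 60%, primary | 90% | 91.8% | 99.6% |

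A null of VE0 = 30% does not fit either: minimum VE 70.7% and 54.2%. Only the 20% null matches. Both minimum VEs and the interim power agree after rounding; the primary power agrees to within two points.

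**Step 3: chance of success over both looks**, calculated exactly from the binomial splits (53 cases, then 52 more).

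| True VE | Rule as written (17/53, 42/105) | 20% rule (14/53, 36/105) |
|---|---|---|
| 20% | 21.6% | 2.5% |
| 30% | 45.4% | 9.6% |
| 60% | 99.6% | 92.0% |

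**Step 4: sensitivity.**
- Exact test of VE = 0: cut-offs 16/53 (VE 56.8%) and 41/105 (VE 35.9%). The two-look chance of success is 16.0% at true VE 20% and 37% at true VE 30%.
- Person-time ratios of 1.5:1 and 2:1 (vaccine to control): the primary cut-off is 33% to 35% for VE0 = 0 and 47% to 48% for VE0 = 20%.
- LD/SD cases enter the analysis but not the trigger, so more than 105 cases may be analysed. Scaling by the Table A1 sizes (an assumption), 105 × 19000/15600 ≈ 128 cases, and the cut-offs become 31.6% and 45.8%.

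**Step 5: alpha split.** A gamma spending parameter of about −2.5 gives 1.13% at information fraction 53/105. With 4.44% at the final look, the overall two-sided level is 0.04997. The split is sound for the null tested.

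**The case against.** The strongest reply is that Section 9.2.1.1 is a valid test of a clear null. Overall Type I error for equal incidence is 5%, as Section 4.1 promises. The 21.6% is the chance of rejecting VE = 0 when the vaccine does have 20% efficacy, so it is not an error under the null that is tested. **This stands.** The plan does not inflate alpha for VE = 0, and the 21.6% is an error rate only if 20% is the hurdle.

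Second, Section 4.1 never writes the 20% threshold as a hypothesis or CI rule. One could read significance (VE above 0) and evidence of efficacy (VE above 20%) as two tiers. The plan does not say so, and its power figures hold only for the higher one. The point shows how the mismatch could have arisen, but does not remove it.

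Third, the CI is reported at the same alpha, so a VE of 33% with a lower limit of about 0.5% would be plain to any reader. That is true and makes the repair easy. It does not settle whether such a result is a success.

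Fourth, 33% is the Wald figure for the primary look under equal person-time, the interim equivalent is about 53%, and at the assumed true VEs of 60% to 70% both rules succeed with over 90% probability across the two looks. All of this is correct. The exact test narrows the gap at the primary look to about 12 points (35.9% against 47.8%) but does not close it. A success rule matters most for results weaker than the plan hopes for.

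**Conclusion.** The concern holds. The power and minimum VE in Section 4.1 derive from a null of VE at most 20%, while the only written success rule tests VE = 0. An observed VE between about 33% and 48% at the primary analysis, or between about 53% and 64% at the interim, would be significant under Section 9.2.1.1 and yet below the stated minimum.

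The cut-offs assume equal person-time, exactly 53 and 105 analysed cases, and an unadjusted Wald interval. The alternatives tried move the primary cut-offs by at most about three points. The covariate-adjusted robust model could shift them slightly, but not enough to account for gaps of about 11 points (interim) and 15 points (primary). This must be fixed because it decides whether the primary efficacy claim succeeds.

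**What to change.** State one null and use it in both sections.

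- **If the 20% threshold is intended**, as the Section 4.1 figures indicate: in Section 9.2.1.1 write H0: VE ≤ 20% (RR ≥ 0.80). Declare success only if the lower limit of the two-sided (1-alpha) CI for VE exceeds 20%, and report the matching Wald test of log RR against log 0.80. Apply the same 20% bound to the exact conditional fallback. Keep the p value for RR = 1 as descriptive.
- **If VE = 0 is intended**: leave Section 9.2.1.1 as it is, remove the 20% threshold from Section 4.1, and restate the minimum VE (about 53% and 33%) and the power (about 95% at VE 70% and above 99% at VE 60%).

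Either choice costs a few lines of SAP text. The first also needs one comparison of a CI limit that is already produced. No new data are required, and under the first option the hurdle becomes the one Section 4.1 already gives. The choice should be recorded before the analysis is unblinded.

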#### **9.2.1.3 Subgroup Analysis of Primary Endpoint**

Subgroup analysis will be performed for the primary efficacy endpoint, the incidence of SARS-CoV-2 virologically-confirmed COVID-19. Within each level of a subgroup, the VE and its corresponding  $(1-\alpha)$  % CI will be estimated using a Poisson regression model with robust variance with the term of treatment. A forest plot of the VE and the  $(1-\alpha)$  % CI will be presented. If the Poisson regression model does not converge for any stratum of a subgroup, the exact conditional method for stratified Poisson regression using PROC GENMOD with the exact statement will be used.

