### **9.2.2.3 Other Secondary Efficacy Endpoints**

The remaining endpoints will be analysed in the same manner as the pooled analysis of the primary efficacy endpoint as described in Section 9.2.1.1 (see Pooled Analysis of Primary Efficacy Endpoint). VE will not be computed unless 5 cases have accrued for the respective endpoint, but the distribution by groups will be presented.

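### For sparse secondary endpoints and subgroups, non-convergence is an unreliable trigger for the exact method when one arm has no cases

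*SAP*

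**What the plan says.** Section 9.2.1.1 sets the method: "A Poisson regression model with robust variance (Zou 2004) will be used as the primary efficacy analysis model", with study, treatment and age group as terms and log period at risk as offset. It is to be "implemented by using the SAS PROC GENMOD procedure for binary data with the REPEATED statement for subject ID and logarithm link". The only route to the exact method is the condition "If the Poisson regression model with robust variance fails to converge, the exact conditional method for stratified Poisson regression".

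Section 9.2.1.3 uses a treatment-only model within each subgroup level. It has the same single trigger, "If the Poisson regression model does not converge for any stratum of a subgroup", and no minimum number of cases.

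Section 9.2.2.3 extends the method to severe disease, hospital admission, ICU and death: "The remaining endpoints will be analysed in the same manner as the pooled analysis of the primary efficacy endpoint". Its only guard is a floor on the total: "VE will not be computed unless 5 cases have accrued for the respective endpoint". It does not require a case in each arm.

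No section has a rule for zero cases in one arm. The confidence level follows the analysis stage: "The planned alpha level is 1.13% for interim analysis and 4.44% for primary analysis" (section 4.1).

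**The concern.** With no cases in the vaccine arm, the maximum-likelihood log relative risk is minus infinity. The likelihood flattens as the coefficient falls, so an algorithm that watches the deviance or the score can stop and report convergence. The sandwich variance then gives no warning: fitted values and residuals in the empty arm are all close to zero, so that arm contributes almost nothing. The SE reflects the control cases alone, and a Wald interval around a log RR of about -21 rounds to 100% at both ends.

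The situation is most likely where an effective vaccine leaves few cases: severe disease, hospital admission, ICU, death, and small subgroups such as one country or adults aged 65 and above. Efficacy against severe disease is the first secondary objective in section 2.2, and section 9.2.1.3 plans a forest plot of subgroup intervals. A handful of cases could be shown there with an interval of no width.

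**Working it through.** **Inputs.** Model, software and trigger: SAP 9.2.1.1 and 9.2.1.3. Floor of 5 cases: 9.2.2.3. Case counts of 53 and 105, and alpha of 1.13% and 4.44%: section 4.1. Two-sided tests: section 7.1. Assumptions: 9,500 participants per arm (half of the roughly 19,000 in Table A1), and person-time 1:1 or, as an alternative, 2:1 vaccine to control.

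**The plan's own figures.** An exact conditional binomial calculation at 1:1 rejects VE 20% with at most 14 of 53 cases in the vaccine arm. Power at VE 70% is 77.4% (plan: 77%), and the minimum observed VE is 1 - 14/39 = 64.1% (plan: 64%). At 105 cases it rejects with at most 36. Power at VE 60% is 91.8% (plan: 90%), and the minimum VE is 1 - 36/69 = 47.8% (plan: 48%). The 1:1 assumption is therefore compatible with section 4.1, though this does not establish the allocation.

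**Why the SE collapses.** In the treatment-only model, each arm contributes (sum of squared residuals)/(sum of fitted values)² to the robust variance of the log RR.
- Control arm, 5 cases: about 5/5² = 0.2.
- Vaccine arm, 0 cases: sum(μ²)/(sum μ)², about 1/9,500 = 0.0001.
- Robust SE: about √0.2 = 0.447, that is, 1/√(control cases).

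**Fits for 0 versus 5 (Python; SAS not available).**

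| Fit or stopping rule | Converged | Log RR | Robust SE |
|---|---|---|---|
| GLM, HC0 variance | yes | -21.3 | 0.447 |
| GEE, one cluster per subject | yes | -22.3 | 0.447 |
| Newton-Raphson, likelihood or gradient rule | yes, 17 to 18 iterations | about -17.7 | 0.447 |
| Newton-Raphson, relative parameter change 1e-4, 50 iterations | no | still falling | not applicable |

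With the GLM values, the upper limit for the log RR is -21.3 + 1.96 × 0.447 = -20.4, so both VE limits round to 100%; z = 21.3/0.447, about 48. The model-based SE at the likelihood-rule stop exceeds 3,000. Adding study and age terms, or using 500 or 2,000 per arm, leaves the robust SE at 0.447 to 0.448. In the last row the coefficient still moves by about 1 per iteration, a relative change of 0.02 at iteration 50. The exact fallback would then fire.

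With 1 versus 4 cases the same model gives VE 75% (-137%, 97%), p = 0.21. With 0 versus 2, which a subgroup could contain, it again reports convergence (SE 0.707), while the exact p at 1:1 is 2 × 0.5² = 0.50.

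**Exact result for 0 versus 5.** If the vaccine-to-control person-time ratio is k, the two-sided p is 2 × (1/(1+k))⁵. The upper limit for RR is (q/(1-q))/k, with q = 1 - (α/2)^(1/5).

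| Person-time | Two-sided p | VE lower limit, 95% | α = 4.44% | α = 1.13% |
|---|---|---|---|---|
| 1:1 | 2 × 0.5⁵ = 0.0625 | 1 - 1.091 = -9% | -14% | -82% |
| 2:1 | 2 × (1/3)⁵ = 0.008 | 1 - 1.091/2 = +45% | 1 - 1.142/2 = +43% | 1 - 1.816/2 = +9% |

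**How often the vaccine arm is empty.** P(0 of m) = (1/(1 + k(1-VE)))^m.
- m = 5, 1:1: (1/1.4)⁵ = 19% at VE 60%; (1/1.1)⁵ = 62% at VE 90%.
- m = 5, 2:1: (1/1.8)⁵ = 5% at VE 60%; (1/1.2)⁵ = 40% at VE 90%.
- m = 53, 1:1: 9 × 10⁻⁷ at VE 70%; 0.6% at VE 90%.
- m = 105, 1:1: about 5 × 10⁻⁵ at VE 90%.

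**The case against.** The strongest reply is that the failure has not been shown in the planned software. Section 9.2.1.1 names PROC GENMOD, and the convergence seen here comes from Python stopping rules. Under a parameter-change rule the model fails to converge, and the plan's fallback does what it should. This stands: a reader might infer that the plan will produce VE 100% (100%, 100%), and neither the document nor these fits establish that. What remains is that the plan fixes no convergence criterion, so the choice between two very different answers is left to a software tolerance.

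A reader might also infer that the primary result is at risk, because the trigger is stated in 9.2.1.1. The document does not support that. The pooled primary analysis runs at 53 or 105 cases, where an empty vaccine arm is very unlikely, and the 5-case floor belongs to 9.2.2.3. The alpha split is tied to the primary endpoint. No success criterion is set for the sparse endpoints or subgroups, so no confirmatory decision turns on them.

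Nor can one say that 0 versus 5 is never significant under the exact method. That holds at 1:1; at 2:1 the doubled p of 0.008 is below both planned alpha levels.

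Finally, an interval of zero width from five cases would look odd to a careful reader. That limits the harm, but a plan should not depend on it.

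**Conclusion.** The point holds for the sparse secondary endpoints of 9.2.2.3 and the subgroup strata of 9.2.1.3. Non-convergence is an unreliable proxy for an empty arm. When it misses one, the output claims certainty (p < 0.0001, both limits 100%) where the exact analysis gives p between 0.008 and 0.0625 and a 95% lower limit between +45% and -9%, for person-time ratios from 2:1 to 1:1. Both exact results are far less certain than the robust output. The situation is realistic: among 5 cases the chance of an empty vaccine arm is 19% to 62% at 1:1, and 5% to 40% at 2:1, for VE from 60% to 90%.

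This rests on the two assumed person-time ratios and on fits outside SAS; GENMOD's behaviour is untested. With the primary analysis practically unaffected, this is a should-fix.

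**What to change.** In 9.2.1.1 and 9.2.1.3, change the trigger to: *If either treatment arm has zero events, or the model does not converge, the exact conditional Poisson method already specified will be used.* Section 9.2.2.3 inherits the change through its reference to 9.2.1.1. When the vaccine arm is the empty one, report the exact lower limit at the applicable confidence level, with an upper limit of 100%. The exact method itself needs no other change.

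The cost is one added condition in two places and a program branch that the fallback already requires. Intervals for these endpoints will be wider, which reflects the information in so few cases.
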